**7. 2. 2 Non-treatment ANC visits**

At ANC visits when treatment is not administered, women will be seen by Health Centre/Hospital staff only. Blood pressure, weight, fundal height and other indicators of maternal health will be recorded. Should women have symptoms or signs warranting further investigation, they will be referred to study staff, and an Unscheduled Visit form will be completed. Women with hypertension will have physical examination and urinalysis to seek other evidence of pre-eclampsia. Study or Hospital physicians will assess women as requested by study and health centre nursing staff.

**7.2.3 Delivery**

At delivery, women will receive standard care from Health Centre or Hospital staff, assisted as necessary by study staff. Maternal venous blood (10 ml) will be collected either before or within 24 hours of delivery. Maternal haemoglobin concentration will be measured, and blood smears prepared. Plasma, PBMCs and red cells will be separated and stored, as detailed in the separate immunology protocol.

Samples will be collected from the placenta, for blood smears, histology and immunological studies. Cord blood samples will also be collected. The baby will be weighed, and gestation assessed using a modified Ballard’s assessment.

**7.2.4 Post delivery infant and maternal follow up**

Women and their babies will be seen at 6 weeks post partum and babies only at 12 months of age. Heel prick blood will be collected at 6 weeks (see also 6.1.5 b). A subset of 250 women will be followed on one further occasion, at 3 months post partum, to provide a further venous blood sample.

## Early Termination Visit

A woman might be terminated early from the study by either withdrawing from the study or by permanently moving outside the study areas. In addition the woman may be terminated from the study following the occurrence of a serious adverse event (SAE see below), that prevents the continued presence of the participant in the study.

In case of an early termination, the date and reason for termination will be noted in the participants’ database. No specific early termination visit will be done. If the woman’s participation is terminated due to a serious adverse event, the termination will also be noted on the SAE forms.

## Criteria for Discontinuation or Withdrawal of a Subject

**Participants may withdraw at any time from participation in this study.**

A participating woman will be discontinued from the study if one of the following criteria are fulfilled:

- the participant moves away from the selected study area for a period longer than 2 months
- the participant develops a chronic illness that impedes continuation in study.
- the participant displays or develops severe side effects to study drugs
- the participant dies.

# Assessment of Outcome MeasureS

## Specification of the Appropriate Outcome Measures

### Primary Outcome Measures

Low birth weight is defined as weight within 7 days birth of <2500 g. For Health Centre or Hospital deliveries, it will be recorded within the first hour of life. For home deliveries, it will be recorded by study staff within 7 days of delivery. Babies will be weighed at study health centres where possible. Otherwise a mobile team will visit them in the village.

### Secondary Outcome Measures

1. ***Prevalence of P. falciparum at 2nd treatment time point and delivery***

The prevalence of *P. falciparum* in peripheral, placental and cord blood films will be determined by light microscopy and PCR-LDR. Prevalence of malaria parasites in placental histology will be determined by light microscopy and (where applicable) immuno-histochemistry. Imprint smears from placenta will be used to assess parasite morphology and assist in speciation.

1. ***Mean maternal hemoglobin concentration at delivery, and proportion of women anaemic (Hb < 11 g/dl).***

Hemoglobin concentration will be determined the Hemacue system. Where applicable confirmation may be done using a Coulter ActDiff system.

1. ***Prevalence of P. vivax at enrolment, second treatment, and delivery***

The prevalence of *P. vivax* in peripheral, placental and cord blood films will be determined by light microscopy and PCR-LDR. Prevalence of malaria parasites in placental histology will be determined by light microscopy and (where applicable) immuno-histochemistry. Imprint smears from placenta will be used to assess parasite morphology and assist in speciation.

1. ***Incidence of symptomatic malaria during pregnancy***

Symptomatic malaria will be monitored through passive case detection at participating health facilities. Symptomatic malaria will be defined as an axillary temperature >37.5°C or a history of febrile illness and (microscopically) confirmed malarial infection of any density.

1. **Proportion of women carrying azithromycin-sensitive sexually transmitted infections at second treatment visit (28-34 weeks).**

The prevalence of *N gonorrhoeae*, *C trachomatis* and *T vaginalis* will be determined by multiplex PCR from self-collected high vaginal swabs.

1. ***Incidence of Adverse Events, including severe adverse events (SAEs), and AEs possibly or probably associated with study medications***

For definitions and procedures of AEs see Section 9 below

1. **Prevalence of drug resistance markers in parasites infecting women in late pregnancy**

The prevalence of molecular markers of SP resistance will be determined in randomly selected, PCR-positive samples using an established PCR-LDR assay.

1. **Prevalence and antibiotic sensitivity patterns of *S. pneumoniae* in nasopharyngeal swabs collected at delivery**

The prevalence of carriage of S pneumoniae and of antibiotic resistance will be determined in nasopharyngeal swabs by routine culture and disc diffusion, respectively. Isolates will be stored for further characterization.

1. ***Maternal, perinatal and infant mortality rates.***

The following mortality rates will be determined:

1. Maternal mortality rate (enrolment to 6 weeks post partum). Determined by home visits to communities where mothers lived, and interview of family members and other relevant individuals.
2. Abortion/stillbirth rates. These are defined as death of a fetus before delivery. Abortion is a death before 22 weeks estimated gestation and stillbirth is a death at or after 22 weeks gestation
3. Perinatal mortality rates. These are defined as death (due to any cause) of a child from 22 weeks to 7 days post partum.
4. Infant mortality rate (0-12 months). All cause infant death will be recorded.
5. **Impact of IPTp on development of immunity to malaria in pregnancy**

A detailed description of immunological outcome measures will be given in a separate immunology sub-protocol.

1. **Characteristics of parasites infecting pregnant women.**

A detailed description of parasitological outcome measures will be given in a separate immunology sub-protocol.

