**Sexually Transmitted Infections in PNG**

Sexually transmitted infections are common in Papua New Guinean women. In previous studies, prevalence of active syphilis has varied from 13.6 to 16.7 %, of chlamydia between 19.3 and 20.0 %, of *Neisseria gonorrhoea* between 10.1 and 15.1 % and Trichomonas between 17.6 and 20.0 %, between 32.1% and 35.5% having at least 1 bacterial STI. These studies were from community studies in non-pregnant, low risk women, and were not from Madang Province. Apart from their effects on the woman’s reproductive health, each of these is associated with adverse fetal outcomes including congenital syphilis, ophthalmia neonatorum, pneumonitis, prematurity and low birth weight. All of the bacterial STIs are susceptible to azithromycin treatment. Trichomonas is also common, and does not respond to azithromycin, but the evidence associating it with adverse pregnancy outcome is less compelling. PNG also has an emerging HIV epidemic. HIV seroprevalence in Madang province is around 2%, and HIV transmission is increased in the presence of genital coinfections. Thus, controlling STIs may have several benefits including improving maternal health and pregnancy outcome and decreasing the potential for HIV transmission.

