Following the collection of data and blood sample women receiving SP + AZ will receive the 2nd IPTp treatment dose, women in the control arm will receive SP and AZ placebos. The first dose will be dispensed directly by the study staff. Pack number, date and time of administration will be recorded on the enrolment forms. The participant will then be instructed how to take the 2nd dose at home.

At the end of the visit the field study team will schedule the next treatment visit with the woman. Women who failed to attend the study ANC clinic will be contacted by the village reporters and encouraged to present at their health centre to receive the missed treatment.

1. Third IPTp Treatment Visit

During the final treatment visit the PNGIMR field study team will conduct the following tasks:

Woman:

- Interview and record
  - history of bednet use in two weeks prior
  - history of malaria treatment in two weeks prior
- Take growth measurements
  - Maternal weight
  - Fundal height
- Collect 250 µl finger prick blood sample (in first 150 women, collect instead 5 ml venous sample for plasma separation and immunological studies).
  - Prepare thin and thick blood smears
  - Archive a portion of the blood sample for laboratory analyses
- Where possible, collect a self-administered high vaginal swab for determination of sexually transmitted infections (STIs)
- Check the woman’s health records booklet for recent health centre visits and record applicable information
- Measure maternal blood pressure and check for oedema. If elevated blood pressure or oedema present, women will be tested for proteinuria. Presence of all three will be considered clinical evidence of pre-eclampsia, and women will be referred for obstetric care through Modilon Hospital.
- Ultrasound will be performed where available to (a) measure fetal growth using bi-parietal diameter, head circumference, abdominal circumference and femur length and (b) document uteroplacental blood flow patterns using color Doppler, as described

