# Study Schedule

**Table 2: Summary of scheduled study activities**

|  |  |  |  |
| --- | --- | --- | --- |
|  |  | **Time** | **Activities** |
|  |  |  |  |
|  |  |  |  |
| **Enrolment Visit** |  | 1st antenatal care visit at < 14 -20 weeks of gestation | - Identification of eligible mother - Enrolment - Baseline Data collection - Collection of venous blood sample - Collection of vaginal swab - Ultra Sounds examination - 1st IPTp treatment |
|  |  |  |  |
| **2nd Treatment Visit** |  | At 22-26 weeks of gestation | - 2nd IPTp treatment - Finger prick blood sample - Collection of data on net use, health seeking, etc - Collection of vaginal swab - Treatment for STIs |
|  |  |  |  |
| **3rd Treatment Visit** |  | At 28-32 weeks of gestation | - 3rd IPTp treatment - Finger prick blood sample - Collection of data on net use, health seeking, etc |
|  |  |  |  |
| **Delivery** |  | At delivery | - Health assessment of mother & child - Measurement of child’s birth weight, & maternal Hb - Collection venous blood & placental blood sample and placental specimen from mother - Cord blood collection from child |
|  |  |  |  |
| **6 Weeks Follow-up** |  | 6 weeks after delivery | - Health assessment of mother & child - Collection of heel prick blood sample from child |
| **3 months follow up** |  | 3 months post delivery (250 consecutive women) | - Health assessment of mother & child - Collection of venous blood from mother |
|  |  |  |  |
| **1 year Follow-up** |  | 1 year after delivery | - Health assessment of child |
|  |  |  |  |

A graphic representation of study activities is given in Appendix I.

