### Secondary Outcome Measures

1. **Prevalence of *P. falciparum* malaria at delivery by microscopy**

This outcome measure will be analysed in women in whom blood films (peripheral and/or placental) are collected at delivery.

1. **Prevalence of *P. falciparum* malaria at delivery by histology**

This outcome measure will be analysed in all women from whom an assessable placental biopsy is collected at delivery.

1. **Maternal Hb at delivery by histology**

This outcome measure will be analysed in all women from whom an Hb measurement at delivery is available.

1. **Incidence of symptomatic malaria**This outcome will be analysed in all women that have had 1 IPTp treatment
2. **Prevalence of STIs on Vaginal swab at 28-34 weeks gestation**

This outcome measure will be analysed in all women in whom an assessable swab is collected at 28-34 weeks. Rates of carriage of N gonorrhoeae, C trachomatis and T vaginalis (assessed by PCR) will be compared between groups.

1. **Maternal, perinatal and infant mortality rates**

All deaths, irrespective of cause of death, occurring in the cohort of pregnant women and their fetuses or children between Enrolment and Final Evaluation Visit (6 weeks post partum for pregnant women, deaths from 22 weeks gestation to 28 days post partum for perinatal mortality, deaths from day 28 of life to 12 months of age for infants) will be considered for this analysis

1. **Reported side effects / Adverse events**

All reported side effects following IPTp treatment, irrespective of total number of treatments a woman received, will be considered for these analyses.

1. **Molecular markers of SP resistance**

This endpoint will be assessed in a random sample of PCR-positive samples collected at 2nd treatment and at delivery.

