## Sample Size Considerations

The primary objective of the study is to determine the effect of IPTp with SP/AZ compared to SP/CQ clearance treatment on prevalence of low birth weight (LBW) in women using ITNs. The overall power and sample size calculations are thus based on this outcome.

The analyses for this primary outcome measure will use Poisson regression (with or without random effects). Sample size calculations for these types of analyses are non-trivial and often require extensive simulations. For that reason we are using an approximate sample size calculation based on comparison of two Poisson rates.

**Table 3**: Sample size calculations for principal outcomes using appropriate two sided tests, a significance level of 5% and a power of 80%.

|  |  |  |  |  |
| --- | --- | --- | --- | --- |
| **End points** | **Expected Outcomes** | |  | **Sample Size** |
|  | Control | AZ-SP |  |  |
|  |  |  |  |  |
|  |  |  |  |  |
| **Primary** |  |  |  |  |
| Prevalence of LBW | 12% | 8.4% |  | 1163 |
| Mean birth weight | 2.94kg | 3.01kg |  | 970 |
|  |  |  |  |  |
| **Secondary** |  |  |  |  |
| Prevalence of *P. falciparum* at delivery (peripheral & placental) by PCR | 30% | 20% |  | 389 |
| Prevalence of malaria in placental histology | 30% | 20% |  | 389 |
| Mean Hemoglobin at delivery | 10.0 | 10.3 |  | 845 |
| Prevalence of bacterial STI at 2nd/final treatment time point | 30% | 10% |  | 72 |
|  |  |  |  |  |

Previous studies suggest that IPTp with SP can increase birth weight by approximately 130 g. ITNs increase birth weight by around 60 g. The effect of adding SP to ITNs is not clear, but we assume that it increases mean birth weight by approximately 70 g. LBW is seen in 16% of babies born to women not using ITNs in PNG. If ITNs decrease LBW by 25% then we will expect 12% of babies to be LBW. SP+AZ may have additional benefits (through control of STIs which impair fetal growth) over SP alone. Our conservative estimate is that SP + AZ will decrease LBW prevalence by 30%. Based on these assumptions, a sample size of 1,163 and 970 women per arm, respectively, are required to find a 30% reduction in LBW and a 70g increase in birth weight with a power of 80% (Table 3).

Assuming, a loss of 20% during follow-up, we will thus enroll 1396 women per arm.

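### STI carriage and perinatal/infant mortality are each defined differently in different sections, so which swabs and which deaths count depends on the section followed

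*Combined protocol and SAP*

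**What the plan says.** **STI carriage, timing.** The lists of secondary outcomes (under Objectives, in 8.1.2 and in 11.1) give the endpoint as "Proportion of women carrying azithromycin-sensitive sexually transmitted infections at second treatment visit (28-34 weeks"). The other sections place the follow-up swab as follows:

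- Table 2 puts the second treatment visit at 22-26 weeks and includes "Collection of vaginal swab - Treatment for STIs". Its third visit, at 28-32 weeks, has no swab.
- Section 6.1.4 has no swab in the second-visit task list. At the third visit it says: "Where possible, collect a self-administered high vaginal swab for determination of sexually transmitted infections (STIs"). The Study Design section also ties the swab to the final treatment dose.
- Table 3 and section 11.4.2 refer to the second or final time point without choosing.
- Section 11.1.3 sets the analysis population: "This outcome measure will be analysed in all women in whom an assessable swab is collected at 28-34 weeks".

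**STI carriage, organisms.** The endpoint is labelled azithromycin-sensitive, and Table 3 is sized on bacterial STI. Sections 8.1.2 and 11.1.3 nevertheless name N. gonorrhoeae, C. trachomatis and T. vaginalis. The Background states: "Trichomonas is also common, and does not respond to azithromycin".

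**Mortality.** On perinatal deaths, section 8.1.2 says: "These are defined as death (due to any cause) of a child from 22 weeks to 7 days post partum". It gives infant mortality as 0-12 months. Section 11.1.3 instead counts "deaths from 22 weeks gestation to 28 days post partum for perinatal mortality, deaths from day 28 of life to 12 months" for infants.

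**The concern.** These are competing rules in current text, not missing detail. Depending on the section followed, a different set of swabs is analysable, the swabs follow a different number of azithromycin courses, a non-susceptible organism may or may not count, and deaths between birth and day 28 fall in different rates.

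A site working from Table 2 would collect swabs that the analysis rule then leaves out. Section 6.3.3 also lets the principal investigators and study coordinator hold the allocation code, so these choices should be closed in writing before outcome data are seen.

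**Working it through.** **1. Swab timing.** Table 2's follow-up swab falls at 22-26 weeks; the analysis window is 28-34 weeks. The overlap is nil and the gap is 28 - 26 = 2 weeks at least. The only Table 2 treatment visit inside the window (28-32 weeks) has no swab.

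Table 2 shows enrolment only to 20 weeks, whereas Study Design enrols to 26 weeks with visits at least 4 weeks apart. The earliest second visit is therefore enrolment + 4 weeks, and the earliest third visit is enrolment + 8 weeks:

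| Enrolled (weeks) | Earliest visit 2 | Earliest visit 3 |
| --- | --- | --- |
| 14 | 18 | 22 |
| 20 | 24 | 28 |
| 24 | 28 | 32 |
| 26 | 30 | 34 |

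A woman enrolled at about 24-26 weeks can have her second visit inside the window. The second-visit label and the 28-34 week rule therefore select different women. In 6.1.4 sampling precedes dosing, so a second-visit swab follows one course and a third-visit swab follows two.

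**2. The plan's own STI sample size.** The inputs are in Table 3: 30% versus 10%, with "Sample size calculations for principal outcomes using appropriate two sided tests, a significance level of 5% and a power of 80"%. For two proportions,

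n = [1.96√(2p̄q̄) + 0.84√(p₁q₁ + p₂q₂)]² / d², with p̄ = 0.20 and d = 0.20.

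This gives (1.109 + 0.461)² / 0.04 = 61.6. The continuity correction, n/4 × [1 + √(1 + 4/(nd))]², gives 71.2, rounded up to 72. Table 3 states 72, so the arithmetic is sound for a bacterial endpoint.

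**3. What pooling T. vaginalis would do (illustration only).** I assume a prevalence t of 17.6-20.0% in both arms, independent of bacterial STI. The figures come from the Background and describe non-pregnant women outside Madang. The pooled rate is 1 - (1 - p)(1 - t).

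| Planning rates | t | Pooled rates | Risk ratio | Consequence |
| --- | --- | --- | --- | --- |
| 30% v 10% | none | 30% v 10% | 0.33 | 72 per arm |
| 30% v 10% | 17.6% | 42.3% v 25.8% | 0.61 | 141 per arm |
| 30% v 10% | 20.0% | 44.0% v 28.0% | 0.64 | 153 per arm |
| 25% v 20% | none | 25% v 20% | 0.80 | power 82% |
| 25% v 20% | 17.6% | 38.2% v 34.1% | 0.89 | power 54% |
| 25% v 20% | 20.0% | 40.0% v 36.0% | 0.90 | power 51% |

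The 25% and 20% rates are the second STI scenario in section 11.2. Power is Φ[(d - 1.96·se₀)/se₁] at 1163 per arm. For 25% v 20% it is Φ[(0.05 - 1.96 × 0.01732)/0.01729] = Φ(0.93) = 82%. For 40% v 36% it is Φ[(0.04 - 1.96 × 0.02013)/0.02011] = Φ(0.03) = 51%. These figures assume a usable swab from all 1163, although 6.1.4 collects swabs only where possible.

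**4. Mortality windows.**

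| Death | 8.1.2 | 11.1.3 |
| --- | --- | --- |
| 22 weeks' gestation to birth | perinatal | perinatal |
| Birth to day 7 | perinatal and infant | perinatal only |
| After day 7, before day 28 | infant only | perinatal only |
| After day 28, to 12 months | infant | infant |

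The documents give no late-neonatal death rate. Assuming 2, 5 or 10 per 1000 among 2 × 1163 = 2326 births, about 5, 12 or 23 deaths would enter or leave the perinatal count.

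**The case against.** Table 2 is only a summary, and section 7.2 sends the reader to 6.1.4 for procedures. Section 6.1.4 and Study Design agree on the final or third visit, and 28-34 weeks recurs throughout the outcome sections. On that view the outliers are Table 2 and the words naming the second visit. This largely stands. A reader might infer from Table 2 that the trial will have no analysable STI swab. The documents do not support that: a late swab is scheduled elsewhere, and some late enrollees reach visit 2 inside the window.

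On organisms, 11.1.3 can be read as comparing each organism separately, and the only sized composite, bacterial STI, already excludes T. vaginalis. That also stands: no section defines a composite that includes it. A reader might infer that the Table 3 comparison is underpowered. It is not, since even the pooled illustration needs 141-153 per arm against an evaluable target of 1163. The label still contradicts the organism list, and at 25% versus 20% pooling would matter.

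On mortality, the objective is to document rates, section 11.4.2 names no test, and the 11.1.3 windows run on from each other, so deaths are reclassified and not lost. A reader might infer a large fall in the infant mortality rate under 11.1.3. Its size cannot be stated, because the documents give no neonatal share of infant deaths. What remains is that two reports of the same rate, each faithful to a section, would differ.

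**Conclusion.** The concern holds as a conflict of definitions in two secondary endpoints. The swab visit, the match between STI label and organism list, and the perinatal and infant windows each differ between sections.

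The firm findings need no assumption: a gap of at least two weeks between Table 2's swab and the analysis window, one azithromycin course against two, and neonatal deaths that move between rates. The dilution figures (risk ratio 0.33 to 0.61-0.64; power 82% to 51-54% at 25% versus 20%) are conditional on a pooling rule the plan does not contain, equal trichomonas prevalence in both arms, and independence. The counts of 5-23 reclassified deaths rest on assumed rates. No effect on the treatment comparison for mortality has been shown, and the primary low-birth-weight analysis is not touched.

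**What to change.** - **Visit.** Correct Table 2 and remove the second-visit wording from the endpoint and from the matching objective, so that the outcome swab is at the final/third visit (28-34 weeks), as in Study Design, 6.1.4 and 11.1.3. Align Table 3 and 11.4.2. State whether a final-visit swab outside 28-34 weeks counts. Table 2 also lists STI treatment at the second visit, while Study Design places it at the final dose; the investigators must reconcile those passages.
- **Organisms.** Define the azithromycin-sensitive endpoint as N. gonorrhoeae or C. trachomatis by PCR. Syphilis is tested at enrolment and is not in the follow-up PCR panel. Report T. vaginalis separately. It should not be presented as a negative control, because section 6.1.8 makes treatment after a positive STI result depend on arm.
- **Mortality.** Use one set of windows in both sections, for example those in 8.1.2: perinatal from 22 weeks' gestation to day 7, infant 0-12 months.

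The cost is protocol wording and one corrected schedule table, with no added visits or specimens. That holds if the change is made before follow-up swabs are taken, since a swab collected at the wrong visit cannot be recovered by redrafting.
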